### Allocation

Two health services each commence the intervention at 3-monthly steps, and as discussed above, randomizing the order of intervention implementation was abandoned for ethical and theoretical reasons. This is now a non-randomized trial, still with a stepped wedge design and cluster intervention. Although not universally accepted, there are precedents for this design in the literature (45) including suggestions for analysis to compensate for the lack of randomization (46). The team's belief is that in a design with three month steps, and an expected time frame of 12 months for maximal effect the detrimental effects of this in terms of potential allocation bias are likely to be outweighed by relational benefits in terms of control and implementation. Services act as their own controls, thus no blinding at service level is either feasible or necessary. Analysis adjusts for the time of commencement of the intervention.

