### Outcomes

The primary outcome measure is a change in the MCH Quality of Care Index (QCI) from aggregated de-identified health service audit data. The MCH QCI provides an indicator for overall adherence to delivering recommended services based on evidence based clinical best practice guidelines in the delivery of care. The MCH-QCI (%) is calculated from audit data as (total number of services provided)/(total number of recommended services) ^*^100 (Table 2) (41). Baseline audit data is collected from services at yearly intervals (over ~1 week at the end of each year) for the 5-year duration of the study. Given the stepped wedge start-time of the intervention, each service will have at least one set of pre-intervention audit data (some up to three) and at least two sets of post-intervention audit data (some up to four; Figure 1). Patients attending the services whose charts may be audited are women with an infant aged between 2 and 14 months at the time of audit, resident in the community for at least 6 months of the pregnancy and using the PHC service as her usual source of care.

**Table 2 T2:** Indicators included in MCH quality of care index.

Maternal Health QCI30 Clinical Indicators	Laboratory investigations: urinalysis (three time points), blood group, antibodies, full blood examination, rubella, Hepatitis B, syphilis serology, HIV, morphology US Physical examination: weight (two time points), body mass index; blood pressure (three time points); fundal height (two time points), fetal heart rate (two time points) History of risk factors: cigarette use, alcohol use, illicit drug use (each at two time points) Antenatal discussions: antenatal education, healthy living (nutrition, exercise, oral health, breastfeeding), psychosocial situation (domestic environment, family support, financial and housing)

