**Figure 1 F1:**
[figure not shown]
Stepped wedge design and participant timeline.

Secondary outcomes: Secondary outcomes will include: (i) percentage of pregnant women having their first antenatal visit before 13 weeks gestation; and (ii) mean birthweight.

Process measures include changes in empowerment for PWG members [measured using the validated Growth and Empowerment Measure (GEM)] (22), alongside a theory-generating process evaluation using qualitative methodology informed by Indigenist and critical theory of the implementation and experience of the intervention (42, 43).

A cost-consequence analysis (CCA) and cost-effectiveness analysis (CEA) will be undertaken from the health system perspective. The outcomes for the CCA will be all primary and secondary outcomes for the study. The outcome for the CEA will be a 100 g increase in mean birthweight (as the main direct health outcome measure).

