### Participant Timeline

The non-randomized cluster stepped-wedge design involves staged implementation of the intervention with two services commencing the intervention planning period at three monthly intervals (Figure 1). Initially, the study was planned to be randomized in terms of the timing of commencement of the intervention, but it became apparent that some of the services were ready much earlier than their allotted start date, based on the pre-existence of a functional women's group. We considered stratified randomization, but ultimately came to the conclusion (with our service partners) that imposing a randomized order on a complex intervention with a presumed theoretical basis of empowerment was likely to be counterproductive in terms of relationship building/engagement with community members and was unpopular with staff at participating services. Thus, randomization of start order was abandoned, and time of commencement will be adjusted for statistically as part of the analysis.

The first phase of the study is the start-up phase and involves study set up, engagement of stakeholders, recruitment of services, recruitment of PWG facilitators, training and formation of PWGs. At the first service engagement meeting in late 2018, services were paired in terms of timing of the intervention for practical reasons based on geographic proximity, to improve feasibility of support (both from the project team and from facilitators at the partner site). The four “early ready” services will embark on the complex intervention first, at three month intervals. The remaining six services have agreed an order of implementation based on perceived readiness (Figure 1). On commencing the intervention, there is a 6-month intervention planning phase comprising the RSF Phase 1 planning workshops and between two and three years for the implementation of MCH improvement plans and monitoring implementation of planned changes (RSF Phase 2) depending on the time of entry.

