### Sample Size

The study is conducted with ten services that have self-nominated and been engaged with MCH audits. The number of maternal records examined in a service at a single audit cycle ranges from <5 to >100, but is usually ~20. Actual mean of the MCH-QCI from 43 services previously involved with One21seventy MCH audits is 65.97% with standard deviation (SD) of 13.58% and a change of 5% is likely to be clinically significant. A stepped-wedge design with five steps, ten clusters and intracluster co-efficient of 0.15 and an average cluster size of 20 has a design effect of 0.40 (with only two baseline and one subsequent audit) (44). Using our expected sample size of 200 audit records from 10 services and a design effect of 0.4 with alpha = 0.05, an SD of 13.58, 99% power is achieved for detecting a 5% change in our primary outcome. This is a conservative estimate. This sample size also gives a statistically significant result if mean birthweight is 100 g higher after the intervention than in the pre-intervention state (e.g., 3.3 kg v 3.2 kg). For the proportion of pregnant women with their first antenatal visit prior to 13 weeks gestation, this study will produce a statistically significant result if the odds of a pregnant woman attending in the first trimester are 1.5 times higher in the PWG group than in the pre-intervention group.

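### The 12-month time frame for the effect ignores the audit look-back: an audit 12 months after start scores only about 7–11% post-planning antenatal care, so a 12-month exposure coding would attenuate the estimate

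*Protocol article*

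**What the plan says.** - **Time to effect.** Allocation gives "an expected time frame of 12 months for maximal effect". Primary and Secondary Outcomes (under Data Collection, Management and Analysis) says of the primary analyses, for both kinds of outcome, that the groups will probably affect outcomes after 12 months from the start at each step.
- **Whose charts.** Outcomes: "women with an infant aged between 2 and 14 months at the time of audit". Audit data are "collected from services at yearly intervals (over ~1 week at the end of each year".
- **What is scored.** The indicators shown in Table 2 concern pregnancy care, for example "fundal height (two time points), fetal heart rate (two time points". One secondary outcome is the "percentage of pregnant women having their first antenatal visit before 13 weeks gestation".
- **Roll-out.** Participant Timeline has "two services commencing the intervention planning period at three monthly intervals", and on commencing "there is a 6-month intervention planning phase comprising the RSF Phase 1 planning workshops". Two to three years of implementation follow. The PWG Complex Intervention spreads the implementation workshops over 8 months.
- **Model.** Linear mixed models with a random community effect and fixed time effects. Neither the exposure variable nor the form of time is defined.
- **Power.** Sample Size claims 99% power for a 5-point change, using SD 13.58 and "intracluster co-efficient of 0.15 and an average cluster size of 20".

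**The concern.** An audit looks backwards. A chart entering at month 12 belongs to a woman who gave birth between month −2 and month 10, and most of the care scored on it was given before planning ended. Maximal effect on care delivered might be plausible at 12 months; maximal effect on these audited outcomes is not. The protocol nowhere accounts for the difference.

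If the primary model treats a service as exposed from month 12, services with little or no exposed care enter as fully exposed. The estimate is then pulled toward zero, and a programme that works could be reported as ineffective.

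**Working it through.** **1. The plan's own figure.** The closed-form stepped-wedge design effect with k=5 steps, b=2 baseline audits, t=1 subsequent audit, n=20 and ρ=0.15 is

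[1+ρ(ktn+bn−1)] / [1+ρ(ktn/2+bn−1)] × 3(1−ρ) / [2t(k−1/k)] = (21.85/14.35) × (2.55/9.6) = 0.404.

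This matches the stated 0.40. Effective N is 200/0.40 = 500, or 250 per arm. SE = 13.58 × √(2/250) = 1.215, and power is Φ(5/1.215 − 1.96) = 98.4%, close to the stated 99%. It assumes that the full 5 points are estimated.

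**2. Exposed share at an audit t months after start.** Assumptions: infant age uniform over 2–14 months; care uniform over the last 6 (or all 9) months of pregnancy; implementation begins at month 6. Births b run from t−14 to t−2.

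At t=12, b runs from −2 to 10, and only births after month 6 contribute:
- six-month care window: (1/12) ∫ from 6 to 10 of (b−6)/6 db = (16/12)/12 = 11.1%
- nine-month window: (16/18)/12 = 7.4%
- planning finished by month 4: (36/12)/12 = 25%
- active from day 0: (36/12 + 4)/12 = 58%
- first-trimester window (b−9 to b−6): it ends at month 4 at the latest, so 0%

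Full exposure needs t−14−6 ≥ 6, so t = 26, or t−14−9 ≥ 6, so t = 29.

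| Audit month | 12 | 15 | 18 | 21 | 24 | 26 | 29 |
|---|---|---|---|---|---|---|---|
| Scored care, six-month window | 11% | 33% | 58% | 83% | 97% | 100% | 100% |
| First-trimester window | 0% | 1% | 21% | 46% | 71% | 88% | 100% |

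**3. Effect on a 12-month indicator.** Five pairs 3 months apart take 12 months to roll out, exactly one audit interval. With yearly audits and a 12-month cut-off, only one audit contains both exposed and unexposed services.

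Example: the first pair starts 6 months after the first of five audits, so follow-up to the last audit is 30–42 months. That equals 6 months of planning plus two to three years.
- At the third audit the pairs are at months 18, 15, 12, 9 and 6. The three coded exposed have shares 58%, 33% and 11% (mean 34%); the other two have about 1% and 0%.
- At the fourth audit all are coded exposed, but the last three pairs are at 97%, 83% and 58%, still rising.
- Generalised least squares with a random service intercept (ICC 0.15, 20 charts per audit) and audit fixed effects gives 0.27 of the true effect: 5 × 0.27 = 1.4 points.

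**4. Range.** The same model with first starts every 0.25 month over the 24 months after the first audit (95 schedules), six-month care window unless stated:

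| Reading | Share of true effect recovered |
|---|---|
| Categorical time, the 24 schedules with first start by month 6 | 27–55% |
| Categorical time, all 95 schedules | −1% to 55% (median 31%) |
| Categorical, all, nine-month care | −6% to 45% |
| Categorical, all, planning done at month 4 | 14–56% |
| Categorical, all, active from day 0 | 32–56% |
| Linear time, all | 33–69% |
| First visit before 13 weeks, categorical, all | −15% to 26% |

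**5. In points and power.** 5 × 0.27 = 1.4 and 5 × 0.69 = 3.5. By the Sample Size method, power is Φ(1.35/1.215 − 1.96) ≈ 20% at 27% of the effect, 62% at 55%, and Φ(3.45/1.215 − 1.96) ≈ 81% at 69%.

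**The case against.** - **The protocol states an expectation, not a coding rule.** The 12-month remark in Allocation serves the argument for dropping randomisation, and the analysis section defines no indicator. Exposure coding is commonly left to the SAP. This stands, and it makes the attenuation conditional. A reader might infer that the bias occurs whatever the SAP does. It does not: audit-date cut-offs at 0, 6, 12, 15, 18, 21 or 24 months recover at most 56% under categorical time, but coding the exposed share removes the bias under its assumptions and is compatible with the model as written.
- **The audit calendar is not known.** Figure 1 is not shown. No single schedule of five audits with a 12-month roll-out yields the stated one to three pre-intervention and two to four post-intervention audits together, and the protocol elsewhere allows more than five audits. A reader might quote recovery of about zero as the headline. That value comes from first starts near month 12, which leave the last pair only 24 months of follow-up, less than planning plus two years.
- **Later audits do capture exposed care.** This is true: the share is 97% at month 24. But by then every service counts as exposed, so categorical time effects absorb much of the gain.
- **Onset may be gradual or early.** Four services already had functioning groups. Onset at day 0 still gives only 32–56%.

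**Conclusion.** The 12-month time frame is wrong for the audited outcomes. Under the stated assumptions a month-12 audit scores 7–11% post-planning care, and no onset considered brings it above about 58%. Full exposure comes at about 26–29 months.

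If exposure is coded from 12 months, the estimate is attenuated under every reading tested that keeps time effects. Recovery is about 27–55% with categorical time and starts that fit the stated implementation period (taking the last audit as study end), lower for later starts or a nine-month care window, and 33–69% with linear time. A true 5-point gain would then be estimated at roughly 1.4–3.5 points, and the 99% power would not be delivered.

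The documents do not support saying that the primary estimate *will* be biased by a fixed amount. The exposure coding, the form of time, the start dates and the shape of onset are all open. The direction is firm; the size is conditional.

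**What to change.** 1. In Allocation, state that the audited antenatal outcomes reach full exposure only about 26–29 months after a service starts.
2. In Primary and Secondary Outcomes, define primary exposure per service-audit as the share of scored antenatal care delivered after planning ended, computed from infant age at audit. Use the first-trimester window for the early-visit outcome.
3. Keep the 12-month indicator, and onset dates such as 0, 4, 9 and 12 months, as sensitivity analyses.

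**Cost.** One figure per service-audit. Infant age is already needed for eligibility, and aggregated data and the health service as unit of analysis can stay. Services with fewer than 5 records may need age bands for confidentiality. The standard error is about 1.3–2.0 times that of the 12-month indicator, but the expected estimate per standard error was higher at every start date tested with onset at the end of planning. The fix removes the bias under its assumptions; it does not restore 99% power, which should be recalculated for this exposure.

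The onset must be assumed, and it is least certain for the four services with existing groups. If true onset is month 4 or 9, the share coding recovers 73–107% of the effect. If it is month 0 or 12, it recovers 37–90%, against −15% to 56% for the 12-month indicator.

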### Data Collection, Management and Analysis

#### Primary and Secondary Outcomes

Cross-sectional data for the primary and secondary outcome measures are collected from services by service staff using the One21Seventy MCH audit tool (35) (from which the MCH-QCI can be obtained) based on evidence-based best practice guidelines about quality MCH care. Processes for conducting these audits and ensuring data quality are well described (3, 7, 41, 47). The MCH-QCI is calculated at the beginning of the study and on an annual basis using existing mechanisms and supports that are part of the inclusion criteria. At least five sets of audit data will be available for each service. This is adequate time to demonstrate significant impacts on quality of care and possibly some health outcomes such as birthweight. Patients attending the services whose charts may be audited are women with an infant aged between 2 and 14 months, resident in the community for at least 6 months of the pregnancy and using the PHC service as her usual source of care.

Data, from which the primary and secondary outcome measures (MCH-QCI) will be drawn, is the property of the PHC service and the service forwards de-identified data to the research team for analysis. This data is in electronic form using a template designed by the research team. This template includes the name and a full description of the variable. Members of the investigator team including the statistician are responsible for checking the templates sent by PHC services and responding to any data queries.

The unit of analysis for the primary outcome is the health service. For the primary analyses (for both primary and secondary outcomes), it is likely that the PWG will have an effect on outcomes after 12 months from the start of the intervention at each step. The outcomes will be analyzed using linear mixed effects models. The models will have a random effect for community, and fixed effects for the effects of time. Estimates of the effect of PWGs will be reported along with 95% confidence intervals. Secondary analyses may adjust for rurality, service size, number of audit cycles and governance structure (ACCHS or government service), and various sensitivity analyses may be undertaken. Statistical significance is set at *p* < 0.05 level to test the hypothesis that there was a significant change in each of the outcome measures from baseline score. Imputation analysis is used to account for the effect of missing data.

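### The single community random effect is adequate for one value per service per audit, but outcomes fitted to records would need a service-by-audit effect, and the 99% power assumes that service effects never change between audits

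*Protocol article*

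**What the plan says.** Under Primary and Secondary Outcomes, the protocol article prescribes linear mixed effects models for the outcomes: "The models will have a random effect for community", with fixed effects for time. The test criterion is "Statistical significance is set at *p* < 0.05 level". The same paragraph makes the health service the unit of analysis, but only for the primary outcome. No unit is given for the two secondary outcomes, first antenatal visit before 13 weeks and mean birthweight. The Outcomes section takes the primary index from aggregated audit data, and Study Participants makes sharing of aggregated service-level data a condition of entry.

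Sample Size works in individual records: "Using our expected sample size of 200 audit records from 10 services". It uses "A stepped-wedge design with five steps, ten clusters and intracluster co-efficient of 0.15", 20 records per audit and a design effect of 0.40, and concludes: "alpha = 0.05, an SD of 13.58, 99% power is achieved for detecting a 5% change in our primary outcome". For first-trimester attendance it speaks of the odds for a pregnant woman, which is a quantity about individuals. It gives one ICC and no correlation between audits of the same service.

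**The concern.** Audits are annual over five years and are done by service staff, and the article itself expects changes of personnel at the services. A service's standing relative to the others may therefore move from one audit to the next.

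A model with a service intercept and fixed time effects has no term for such movement. Fitted to records, it treats some 20 charts from one audit as independent once the service mean and the common time effect are known. The standard error of the intervention effect is then too small, and a chance shift in a few services in one audit year could be reported as an effect of the women's groups. A sample size built on a single ICC makes the same assumption, so its power is too high if service effects move.

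Whether the error rate suffers depends on what is fitted, records or service-by-audit values. The article settles that for the primary outcome only.

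**Working it through.** **Inputs from the protocol article.** Sample Size: 10 services, 5 steps, 2 baseline audits, 1 audit per step, n = 20 records per audit, ICC ρ = 0.15, SD 13.58, difference 5 points, alpha 0.05 (taken as two-sided). Outcomes and Primary and Secondary Outcomes: at least five annual audits, one to three of them before the intervention.

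**Assumed.** The correlation r between a service's effects at two audits. A single ICC implies r = 1; the range tried is 1.0 to 0.5.

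**1. The stated power reproduces.** The standard stepped-wedge design effect, with k = 5, b = 2, t = 1, is

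[1 + ρ(ktn + bn − 1)] / [1 + ρ(ktn/2 + bn − 1)] × 3(1 − ρ) / [2t(k − 1/k)]

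= (1 + 0.15 × 139) / (1 + 0.15 × 89) × 2.55 / 9.6 = 21.85 / 14.35 × 0.2656 = 0.404, against 0.40 stated.

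With 100 / 0.4 = 250 effective records per condition, SE = 13.58 × √(2/250) = 1.215 and 5 / 1.215 = 4.12. Power = Φ(4.12 − 1.96) = 98.4%, against 99% stated.

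**2. Variance components.** Total variance 13.58² = 184.4. Between services: 0.15 × 184.4 = 27.66. Between records: 0.85 × 184.4 = 156.75, which is 7.84 for a mean of 20. If the service effect has between-audit correlation r, the service-by-audit variance is g = 27.66(1 − r).

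**3. Type I error, model fitted to records with a service intercept only.** The true variance of a service-audit mean around its service is 7.84 + g. The model spreads g over the record residual and uses about (156.75 + g)/20. The test statistic is inflated accordingly, and

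type I error ≈ 2Φ(−1.96 √(model variance / true variance)).

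| r | g | model variance | true variance | type I error |
|---|---|---|---|---|
| 1.0 | 0 | 7.84 | 7.84 | 5.0% |
| 0.95 | 1.38 | 7.91 | 9.22 | 6.9% |
| 0.9 | 2.77 | 7.98 | 10.60 | 8.9% |
| 0.8 | 5.53 | 8.11 | 13.37 | 12.7% |
| 0.6 | 11.07 | 8.39 | 18.90 | 19.2% |
| 0.5 | 13.83 | 8.53 | 21.67 | 21.9% |

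A full sandwich calculation, over several crossover patterns allowed by one to three pre-intervention audits, agrees to within about half a point. Simulation (1,200 null trials per setting, REML, z test) gives 11.4-13.3% at r = 0.8 with equal audits. At r = 0.5 it gives 22-23% with equal audits and up to about 27% with unequal service sizes of 5 to 60.

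The ICC matters too. The article gives none for birthweight or attendance. With an assumed ICC of 0.05 and r = 0.8, and total variance scaled to 1, g = 0.01, model variance = 0.96/20 = 0.048 and true variance = 0.0475 + 0.01 = 0.0575. Type I error is then about 7%.

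**4. Type I error, same random effect fitted to one value per service per audit.** The residual is now the service-by-audit variation plus sampling error, so its variance is estimated directly. Simulated type I error over r = 1.0 to 0.5 is 4.8-7.3% with a z test and 4.0-6.1% with a t test (35 degrees of freedom for five audits: 50 − 10 − 5).

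**5. Power when r is below 1.** Layout: five steps of two services, two baseline audits (seven audits), 20 records each, generalised least squares with the service-by-audit variance included, power = Φ(5/SE − 1.96). With equal audits this is the same whether records or service-audit means are analysed.

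| r | SE | power |
|---|---|---|
| 1.0 | 1.22 | 98% |
| 0.9 | 1.41 | 94% |
| 0.8 | 1.58 | 89% |
| 0.6 | 1.85 | 77% |

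The standard error at r = 0.8 is 1.58 / 1.22 = 1.29 times that at r = 1.

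**The case against.** A reader might infer that the primary analysis has a type I error of 13-19%. The documents do not support that. The unit for the primary outcome is the health service and its data are aggregated. With one value per service per audit, no further random effect could be separated from the residual, and the error rate is near nominal. A record count in a sample size formula does not define the analysis model. This objection stands in full for the primary outcome.

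A reader might also infer that the secondary outcomes are certainly fitted to records. That is not stated either: a percentage and a mean birthweight can both be service-audit summaries. What stands is that no unit is fixed for them, while the odds in Sample Size point to individuals.

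The 13% and 19% need correlations of 0.8 and 0.6 that appear nowhere in the documents, and the personnel changes mentioned come with no effect on audit scores. The figures are therefore assumptions within a range that starts at 5%.

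Finally, the article does not say that community is the only random effect, and an analysis plan may add terms or small-sample degrees of freedom. That is fair, and their absence is not the criticism. The point concerns what the article does fix: one model for all outcomes, a unit for only one of them, and a power figure that the single ICC ties to constant service effects.

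**Conclusion.** The point holds in a conditional form.

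- **Primary outcome, one value per service per audit:** the stated random effect is adequate for the type I error, at about 4-7%.
- **Any outcome fitted to records:** the model assumes constant service effects. At ICC 0.15 and 20 records per audit, type I error is about 7% at a between-audit correlation of 0.95, 9% at 0.9, 13% at 0.8 and 19% at 0.6. It is lower if the ICC is lower.
- **Stated power:** 99% reproduces (98.4%) only under constant service effects. In the protocol's own five-step, two-baseline layout it is about 94% at 0.9, 89% at 0.8 and 77% at 0.6, at either unit.

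The between-audit correlation is assumed throughout. The crossover patterns behind the error rates are also assumed, within the stated one to three pre-intervention audits, because Figure 1 is not shown; the error rates hardly depend on the pattern.

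**What to change.** 1. State the unit of analysis for every outcome. Keep the service-by-audit value as the unit for the primary outcome, and test the intervention effect against a t distribution with small-sample degrees of freedom.
2. For every model fitted to records, add a random service-by-audit effect and use Kenward-Roger or Satterthwaite degrees of freedom. Index the effect by annual audit, the occasion on which data are collected.
3. Restate the power with the same correlation structure over a range of between-audit correlations, for example 1.0 to 0.6, and say which value is judged plausible and why.

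This changes wording and requires one recalculation, with no new data. The price is wider intervals, with the standard error up by about 30% at a correlation of 0.8, and a stated power below 99%.

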## Introduction

The health, social and economic outcomes for Aboriginal and Torres Strait Islander Australians continue to be substantially worse than for other Australians (1–3). In Australia, improving the quality and consistency of PHC provided to Aboriginal peoples and Torres Strait Islanders is an essential part of the Australian Government's Close the Gap program (4). Maternal and child health (MCH) is consistently named a priority area by Aboriginal and Torres Strait Islander peoples, policy makers health service providers, and researchers (5, 6). Although Aboriginal and Torres Strait Islander infant mortality rates and the proportion of low birth weight babies born are falling, they remain almost double those of non-Indigenous infants (1).

Internationally, primary health care (PHC) is recognized as critical to addressing inequities in health status (2, 3). While Indigenous PHC services [both Aboriginal Community Controlled Health Services (ACCHS) and government services] provide PHC for Indigenous people, the quality of care and health outcomes can vary significantly between services (3, 7).

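### The p < 0.05 rule tests change from baseline, but the model in the same paragraph estimates a time-adjusted effect of the women's groups

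*Protocol article*

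**What the plan says.** All of this is in the protocol article.

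- **Model** (Data Collection, Management and Analysis, Primary and Secondary Outcomes): "The models will have a random effect for community, and fixed effects for the effects of time". The next sentence reads "Estimates of the effect of PWGs will be reported along with 95% confidence intervals". The model sentence names no intervention term; the second sentence only implies one.
- **Significance rule** (same paragraph): the 0.05 level is set "to test the hypothesis that there was a significant change in each of the outcome measures from baseline score". This is the only hypothesis the paragraph states, and it covers the primary and the secondary outcomes.
- **Primary outcome** (Outcomes): "The primary outcome measure is a change in the MCH Quality of Care Index (QCI", with no reference to a contrast between exposed and unexposed periods.
- **Start time** (Allocation): "Analysis adjusts for the time of commencement of the intervention". Participant Timeline says the same.
- **Sample size** (Sample Size): "Using our expected sample size of 200 audit records from 10 services and a design effect of 0.4 with alpha = 0.05", giving 99% power for a 5-point change.

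**The concern.** A stepped wedge separates intervention from calendar time by comparing services that have started with services that have not, at the same calendar time. A test of change from baseline makes no such comparison. It adds together the PWG effect and whatever else moved the outcome over the study.

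Some background movement is plausible here. Auditing of maternal and child health care is an inclusion criterion, and the Introduction presents audit and feedback as a way to improve care. The Introduction also says that, nationally, "the proportion of low birth weight babies born are falling", which bears on mean birthweight, a secondary outcome.

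The adjustment for time of commencement does not settle the matter. Start time is fixed within a service, so as a main effect it cannot take a calendar trend out of that service's change from its own baseline. If the significance sentence were followed as written, the trial could report success on a trend that PWGs did not cause.

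**Working it through.** **Inputs.** From Sample Size: SD 13.58, intracluster correlation 0.15, 20 records per service per audit, 10 services, five steps, two baseline audits and one audit per step, alpha 0.05. From Allocation: two services start every 3 months. From Primary and Secondary Outcomes: annual audits, at least five per service. Assumed: two-sided tests, a zero PWG effect, and a linear QCI trend shared by all services.

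**1. The plan's own figures.** The standard stepped-wedge design effect (Woertman formula) with k = 5, b = 2, t = 1, n = 20, ρ = 0.15 is

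[1 + ρ(ktn + bn − 1)] / [1 + ρ(ktn/2 + bn − 1)] × 3(1 − ρ) / [2t(k − 1/k)]

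= (21.85 / 14.35) × (2.55 / 9.6) = 0.404, against the stated 0.40.

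The effective sample is 200 / 0.40 = 500, or 250 per condition. SE = 13.58 × √(2/250) = 1.21, and power for 5 points is Φ(5/1.21 − 1.96) = 98.4%, against the stated 99%. The figures reproduce within rounding.

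**2. Which effect was sized.** In the layout behind that formula (seven periods, 20 records per service per period), generalized least squares with fixed time effects gives the PWG coefficient an SE of 1.22 and power of 98.4%. The sample size therefore belongs to the time-adjusted PWG effect, not to change from baseline.

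**3. Literal rule, simplest case: last audit against first.** Five annual audits span four years, so 1 point per year is a 4-point change and 0.5 points per year is a 2-point change.

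If a service's own level is perfectly correlated between audits:
- Variance = 2 × (0.85 × 13.58² / 20) / 10 = 1.57, SE 1.25.
- P(significant) = Φ(4/1.25 − 1.96) = 89%, and Φ(2/1.25 − 1.96) = 36%.

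If that correlation is 0.8:
- Added variance = 2 × (0.15 × 13.58² × 0.2) / 10 = 1.11; total 2.67, SE 1.64.
- P(significant) = 69% and 23%.

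**4. Literal rule, all audits used.** This is generalized least squares on service-by-audit means with a random service effect, comparing before with after and no time effects. Figure 1 is not shown, so several calendars were tried: first start 3 to 12.5 months after the first audit, and an effect lag of 0 or 12 months.

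| Trend per year | 5 audits | 6 audits |
|---|---|---|
| 0.5 points | 26-34% | 37-54% |
| 1 point | 75-87% | 91-98% |

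In the compressed seven-period layout of step 2, with periods 3 months apart, rejection is 9%, 22%, 65% and 94% for 0.5, 1, 2 and 3 points per year.

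**5. The model as stated.** With fixed time effects included and the PWG coefficient tested, rejection is 5.0% in every layout for every shared trend tried, from 0 to 3 points per year.

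**The case against.** The strongest reply is that the significance sentence is loose wording and the model governs. The paragraph includes "fixed effects for the effects of time" and promises PWG effect estimates. Sample Size compares the PWG group with the pre-intervention group and uses a stepped-wedge design effect. On that reading, change is shorthand for the PWG effect and a shared trend is absorbed.

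Much of this stands. A reader might infer that any background improvement would count as a significant result, or that the plan has thrown away the design's protection against trend. The documents support neither. The time effects are in the stated model, and even under the literal rule rejection depends on the size of the trend.

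Three further limits are fair. The last-against-first contrast in step 3 is not an analysis the protocol specifies; it illustrates the literal wording. No QCI trend is given, and the Introduction's falling rates are national infant mortality and low birth weight, not the QCI. Some later services have auditing delays, so steady improvement through auditing cannot be assumed for all of them.

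One could add that a formal null hypothesis is normally left to the analysis plan. That would excuse silence. Here the protocol does state a hypothesis, and it states the wrong one for its model.

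**Conclusion.** The point holds as an internal contradiction: one paragraph estimates a time-adjusted PWG effect and ties significance to a different quantity. The consequence is conditional. Under the literal rule with no PWG effect and five annual audits, roughly 70-90% of trials would reach significance at an assumed 1 point per year and roughly 23-36% at 0.5. If the p-value is attached to the PWG coefficient in the stated model, the figure is 5% for any trend shared by all services. It cannot be said that the trial will declare success on trend alone, only that the current wording would allow it.

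The choice matters in practice because the two tests may well disagree. With all starts inside about a year and annual audits, the time-adjusted effect has only about 53-72% power for 5 points in the calendars tried.

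The results rest on normal tests, 20 records per audit, a constant service effect (except where 0.8 is used) and a linear shared trend. Services start in order of readiness, so trends that differ between early and later services could still bias the time-adjusted estimate.

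**What to change.** 1. Name the PWG exposure term explicitly in the model sentence, alongside the service and calendar-time effects.
2. Replace the significance sentence with: the null hypothesis for each outcome is that the PWG exposure coefficient is zero in the model with service and calendar-time effects, tested at the 0.05 level.
3. State that crude change from baseline is descriptive only.
4. Acknowledge that, with start order set by readiness, the time effects remove only trends common to all services.

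The cost is a few sentences, with no change to data collection or sample size. It should be settled before outcome data are analysed, because it defines success for the primary outcome.
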